#### Blinding

No attempt is made to blind parents or clinicians to the allocation group due to the extended duration of the intervention, and inability to blind carers and parents to the allocated group. However, assessors of primary outcome, and data analysts will perform their assessment and analyses blinded to study group allocation. Parents will be instructed not to inform assessors of their infant’s study group when they attend for follow-up assessment. Data collection will be performed by research staff uninvolved in clinical care of the infants. Analyses will be performed by a statistician independent of the trial research staff and investigators. Interim results will only be shared with the DSMC.

### Data collection methods

#### Data collection methods

Study staff are trained in data entry by the clinical trial coordinator prior to commencing data entry. Outcome assessments use validated data instruments as described in section 16. The collected data will include (but not be limited to) the following screening and baseline data categories in addition to the outcomes described previously.

Eligibility and randomisation data.Maternal demographic data.Infant baseline demographic data.Randomisation data.

The statistical analysis plan (SAP) for the main study and for each of the key secondary studies will detail the baseline and screening data to be included in the final trial report.

#### Plans to promote participant retention and complete follow-up

Strong links with trial participants and their families will be maintained through trial updates, birthday cards for trial participants and regular e-newsletters. Families will be informed about intent to continue multimodal assessments that target a range of potential outcomes that may be influenced by this perinatal intervention, and consent to contact them for potential involvement of their child in such future studies will be obtained.

### Data management

CIRCA DIEM study investigators at each site will be responsible for data collection from medical notes (mother and infant), parents, and bedside clinical charts. Data collection will primarily use a custom-built database in the REDCap designed and managed by the Trial Management Group.^45^ Paper case report forms (CRF) will be used for bedside collection of 24-hour monitoring data and consents as appropriate and digitised for storage. Electronic CRFs will be checked for completeness and accuracy by the research team against source data and verified by the Trial Management Group. All data will be securely stored for the minimum period as per local legislated requirements (normally 15 years for parental data, 25 years for infant participants). Data will be securely destroyed/deleted after mandatory retention periods expire unless consent has been obtained to retain the data for follow-up studies that extend into later adult life of infant participants.

### Statistical methods

#### Statistical methods for primary and secondary outcomes

A separate detailed SAP for the core CIRCA DIEM study outcomes will be produced by a blinded trial statistician and finalised prior to completion of the recruitment phase. Additional SAPs may be published ahead of database lock for the analyses of CIRCA DIEM substudies. Reported results will be in accordance with Consolidated Standards of Reporting Trials (CONSORT) guidelines. Estimands will be constructed for all outcomes and detailed in the SAP. In brief, continuous outcomes will be analysed using either the Wilcoxon-Mann-Whitney test or linear mixed effects regression, binary outcomes using logistic regression and time-to-event outcomes using proportional hazards models, adjusting for the covariates listed above. The false discovery rate employed for all secondary analyses will use the Benjamini-Hochberg algorithm.

After the final database lock, data will be analysed in R Statistical Programming software^44^ using the principle of intention to treat by the blinded trial biostatistician ([name]). Comparability of study groups at baseline will be based on summaries of participant demographic data. Descriptive statistics will include mean (SD), median (IQR) for continuous variables with symmetric and asymmetric distributions, respectively, and counts/percentages for categorical variables.

##### Primary analysis

Standardised cognitive scores will be compared between the intervention and control group at 24 (20–36) months cPNA (primary outcome) using the Wilcoxon-Mann-Whitney test and summarised using the median of differences (Hodges-Lehmann estimator), with asymptotic 95% CI. The primary estimand will be detailed in the SAP, excluding non-randomised siblings from multiple births. In brief, missing primary outcome data due to death will be replaced with a score of 55 (corresponding to –3 SD), or with a score of 40 (–4 SD) in a sensitivity analysis. Missing data, including incomplete Bayley-4 scores, scores outside time window and those missing due to LTFU or withdrawal will be imputed (Amelia II R package) using prematurity strata and multiple birth as predictors.^46^ A separate estimand will be defined for the primary outcome excluding participants with all-cause missing data.

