### Trial design

The CIRCA DIEM is an Australasian multicentre (11 sites), two-arm, parallel-group, prospective, randomised, open, blinded-endpoint (PROBE) superiority trial undertaken in a broad group of infants at highest risk for prolonged chronodisruption (very and extremely preterm infants) with a primary neurodevelopmental outcome (cognition). The participant flow chart for the study is shown in figure 1.

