### Sample size

The initial sample size for the CIRCA DIEM study planned to recruit up to 954 babies to have over 90% power to detect a meaningful change in cognitive score of 4 points, which we defined as the lowest difference considered sufficient to promote a change in clinical care. A sample size re-estimation was planned at 75% completion of recruitment.

Sample size is based on a median difference of 4 points in the primary outcome (standardised cognitive score on the Bayley-4). The standardised score for cognition on Bayley-4 in the general population is designed to have a mean of 100 with an SD of 15.^29^ However, asymmetric distributions may be observed in the trial population. A planned sample size re-estimation was performed after 75% participants had been recruited, using simulation in the sim.ssize.wilcox.test function from the MKpower package.^44^ With the revised sample size of 624 (312 in each group), the study has 90% power to detect an absolute median difference in standardised cognitive score on Bayley-4 of at least 4 points, assuming a score of 85 (corresponding to –1 SD) and SD of 15 in the control group. The CIRCA DIEM study will recruit at least 868 infants (434 in each group) to allow for an anticipated 10% loss to follow-up (LTFU), and an incidence of multiple birth of 20%.

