### Randomisation

#### Sequence generation

Computer-generated randomisation tables were developed and uploaded by the study biostatistician ([name]) from The Kids Research Institute Australia (The Kids), Perth Australia. Treatment allocations were generated using random permuted block sizes, stratified by study centre and gestational age (<28 weeks’ PMA vs 28.0 to <32.0 weeks’ gestation), maintaining 1:1 randomisation of infants to each study group.

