##### Secondary analysis

Standardised cognitive scores will also be compared between the two intervention groups using linear mixed effects regression, with partial clustering for multiple births, adjusted for socioeconomic status, parental risk index, sex, birth weight z-score, prematurity strata, antenatal and postnatal steroid use, multiple birth, key neonatal morbidity count and site. Missing data will be imputed or substituted as detailed for the primary estimand.

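### The primary Wilcoxon-Mann-Whitney test does not account for the centre and gestational-age strata used in randomisation, so it is mildly conservative to the extent that those strata are prognostic

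*Protocol article*

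**What the plan says.** In the protocol article, the Sequence generation section states: "Treatment allocations were generated using random permuted block sizes, stratified by study centre and gestational age", with the gestational-age split at 28 weeks and 1:1 allocation. The Trial design section describes the trial as "Australasian multicentre (11 sites), two-arm, parallel-group", so there are up to 11 × 2 = 22 strata.

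The Primary analysis section compares cognitive scores "using the Wilcoxon-Mann-Whitney test and summarised using the median of differences (Hodges-Lehmann estimator), with asymptotic 95% CI". It names no strata. It excludes non-randomised siblings, scores deaths as 55 and imputes other missing scores, with prematurity stratum as one of the predictors.

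The Secondary analysis section is the only place where the strata are adjusted for. Its mixed model includes prematurity stratum and also "antenatal and postnatal steroid use, multiple birth, key neonatal morbidity count and site".

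The general paragraph on statistical methods mentions adjustment for covariates listed earlier. No such list comes before it, and a Wilcoxon-Mann-Whitney (WMW) test takes no covariates.

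**The concern.** Blocking within strata balances between-stratum differences in outcome across the arms. The null variance of the pooled WMW statistic is derived as if any split of the infants were equally likely, so it still counts that variation as noise. When the strata are prognostic, the statistic therefore varies less than its stated standard error implies. The test then rejects too seldom under the null, and the matching interval is too wide.

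The article gives some reason to think the strata matter: it uses prematurity stratum to impute the primary outcome and adjusts for stratum and site in the secondary model. Deaths scored 55 would widen the gap between strata if mortality is higher below 28 weeks, but no death rates are given. Siblings are excluded from the primary estimand, so sibling clustering does not push the variance the other way.

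At stake are the calibration of the p-value and interval that decide the trial, and a little precision that stratification has already bought.

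**Working it through.** **1. Reproduce the plan's sample size.** The Sample size section says: "With the revised sample size of 624 (312 in each group), the study has 90% power", for 4 points, SD 15. Alpha is not stated there; two-sided 0.05 is assumed from the 95% interval.
- Two-sample formula: (1.96 + 1.2816)² × 2 × 15² / 4² = 295.5, so 296 per arm. Dividing by the Wilcoxon efficiency 3/π gives 310 per arm (620 in total).
- Noether's formula: P = Φ(4 / (15√2)) = 0.5748, and N = (1.96 + 1.2816)² / [3 × (0.0748)²] ≈ 626.
- Power at 312 per arm, using 3/π, is 90.2%.
- Inflation: 624 / 0.9 / 0.8 = 866.7, against 868 stated.

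The figures reproduce with an unstratified WMW test and one overall SD of 15.

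**2. Assumptions for the check.** The article gives no prognostic strength for the strata. Assumed: a gap g between gestational-age strata of 0 to 10 points, a between-centre SD c of 0 to 4, 40% of infants below 28 weeks, unequal centre sizes, blocks of 4, and total SD held at 15. The share of variance explained is R² = (0.24 g² + c²) / 225, where 0.24 = 0.4 × 0.6. For example, g = 8 and c = 3 give (15.36 + 9) / 225 = 10.8%.

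**3. Simulation with 624 infants in 11 × 2 strata** (per scenario: 6,000 null runs, 2,500 power runs, 500 interval runs). Power is for 4 points. The interval ratio is the mean Hodges-Lehmann width divided by the width implied by the estimate's actual spread.

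| g, c | R² | Type I error: WMW / van Elteren / aligned rank | Power: WMW / van Elteren / aligned rank | Interval ratio |
|---|---|---|---|---|
| 0, 0 | 0% | 0.053 / 0.052 / 0.052 | 0.904 / 0.888 / 0.900 | 4.84/4.83 = 1.00 |
| 3, 1 | 1.4% | 0.049 / 0.052 / 0.050 | 0.891 / 0.887 / 0.896 | 4.81/4.64 = 1.04 |
| 5, 2 | 4.4% | 0.041 / 0.044 / 0.046 | 0.900 / 0.894 / 0.906 | 4.83/4.71 = 1.03 |
| 8, 3 | 10.8% | 0.038 / 0.046 / 0.048 | 0.908 / 0.917 / 0.926 | 4.82/4.49 = 1.07 |
| 10, 4 | 17.8% | 0.032 / 0.052 / 0.051 | 0.926 / 0.944 / 0.952 | 4.79/4.49 = 1.07 |

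The Monte Carlo standard error of a type I error near 0.05 is √(0.05 × 0.95 / 6000) = 0.003, so the first two rows cannot be told apart from nominal. The interval ratios are each uncertain by about 1/√(2 × 500) = 3%. They show a rough size only.

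**4. Closed-form cross-check.** With perfect balance the statistic's SD shrinks to √(1 − R²), so the actual type I error is about 2[1 − Φ(1.96/√(1 − R²))]. This gives 0.048, 0.045, 0.038 and 0.031 for R² = 1.4%, 4.4%, 10.8% and 17.8%, close to the simulated values.

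**5. Adding deaths scored 55** (assumed 2% in the older stratum, 12% or 15% in the younger). With g = 5, c = 2 and 12%, type I error is 0.044 for WMW against 0.050 for both stratified tests, and power is 0.835 / 0.838 / 0.844 in the order above. With g = 8, c = 3 and 15%, type I error is 0.033 against 0.049, and power is 0.815 / 0.833 / 0.838. The interval ratios are 5.30/5.33 = 0.99 and 5.40/5.08 = 1.06.

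**The case against.** The strongest reply is that nothing here is an error. The WMW test remains valid, the trial was sized with the same unstratified test and a single SD of 15, and the secondary mixed model already adjusts for stratum and site. All of that stands. It also stands that every magnitude rests on assumed prognostic strength.

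A second reply is that the usual stratified test gains little. This also stands. Across simulated settings with prognostic strata, van Elteren over up to 22 cells often changed power by under a point in either direction. With a 6-point gap, no centre effect and deaths of 15% and 2%, power was 81.4% for WMW and 81.5% for van Elteren. With uninformative strata it lost 0.904 − 0.888 = 1.6 points. The Trial status section says that sites were added over time, so some cells may be small. This argues against that particular remedy. The aligned-rank test lost only 0.904 − 0.900 = 0.4 points with uninformative strata, within simulation error.

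A third reply is that the analysis plan, which is not shown, may specify a stratified version. It may, and the article leaves the estimand to it. But the article itself names the test, estimator and interval, so a stratified version would alter what is written.

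A reader might infer more than the documents support:
- **That the false-positive rate is inflated or the estimate biased.** The error runs the other way, and the estimate is not biased by it.
- **That the trial falls short of 90% power for this reason.** Without deaths, simulated WMW power stays at about 89% to 93%. The lower power in step 5 affects all three tests and comes from the assumed deaths.
- **That the test is conservative whatever the data.** With uninformative strata there is no effect.

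**Conclusion.** The mismatch between the stratified randomisation and the unstratified primary test is clear in the article. Its consequence is conditional and modest. Over the assumed range of prognostic strata, actual two-sided type I error is roughly 3% to 4.7% (close to nominal when the strata explain only about 1% of the variance), and the interval is roughly 2% to 7% too wide, or about 0.1 to 0.3 points on a width of about 4.8. An aligned-rank test would gain 0.6, 1.8 and 2.6 points of power when the strata explain 4.4%, 10.8% and 17.8% of the variance.

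These figures depend on the assumed gestational-age gap, centre SD, stratum mix and death rates, none of which the article supplies. The validity of the test, the absence of bias and the stated 90% power are not in question. The change is worth making because it is cheap and affects the analysis that decides the trial.

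**What to change.** Make the primary analysis a rank test that conditions on the randomisation strata and loses little if they are uninformative. Two suitable forms are an aligned-rank test, or the ordinary Wilcoxon rank-sum statistic with its null mean and variance computed within centre by gestational-age stratum. Report the matching aligned or stratified Hodges-Lehmann estimate and 95% interval. Prespecify how very small centres are pooled and how results are combined across the multiple imputations. Keep the unstratified WMW test as a sensitivity analysis. Plain van Elteren over all 22 cells is less suitable, for the reason given above. Correct the reference to a covariate list that does not appear.

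The cost is analysis-plan wording and code, including the step across imputations, and a pooling rule. No further infants are needed. The Trial status section expects outcome collection to run to early 2029, so the change can be fixed while the statistician is still blinded.

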### Methods in analysis to handle protocol non-adherence and missing data

Compliance with prescribed light and sound levels recorded at each site and timepoint relative to randomisation, will be reported for the whole cohort and separately for night/day for each stratum and each treatment group.

The handling of missing data will be based on the reason for missingness and documented for each estimand in the SAP. In general, we will employ the Amelia II R package for the multiple imputation of multivariate incomplete data, which uses an algorithm that combines bootstrapping and the expectation-maximisation algorithm.^48^

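### Bayley-4 assessments left incomplete because of cognitive impairment would be imputed like ordinary loss to follow-up, and no described analysis gives such a child a low score

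*Protocol article*

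**What the plan says.** In the protocol article, Primary analysis gives two routes for a missing cognitive score. A death is scored 55, or 40 in a sensitivity analysis. For everything else: "Missing data, including incomplete Bayley-4 scores, scores outside time window and those missing due to LTFU or withdrawal will be imputed", with the Amelia II package, "using prematurity strata and multiple birth as predictors". Incomplete assessments are therefore named, and placed with out-of-window scores, loss to follow-up and withdrawal.

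The section describes one further estimand: "A separate estimand will be defined for the primary outcome excluding participants with all-cause missing data". For the mixed model, the Secondary analysis section says: "Missing data will be imputed or substituted as detailed for the primary estimand".

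The section on non-adherence and missing data sets the general principle: "The handling of missing data will be based on the reason for missingness and documented for each estimand in the SAP".

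**The concern.** The outcome is cognition. A child whose cognitive impairment prevents completion of the test has a missing score because the score would be low. Loss to follow-up need not carry that information. With two predictors, a severely impaired singleton below 28 weeks looks the same to the imputation model as every other singleton below 28 weeks.

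Such children can be in the trial. The exclusion criteria remove congenital neurodevelopmental abnormality but not acquired brain injury, and grade 3 or 4 intraventricular haemorrhage and periventricular leukomalacia are listed as in-hospital outcomes.

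At stake is a difference between arms in severe impairment. If it shows up partly as untestable children, the primary analysis will understate it in either direction. If imputed scores also feed the secondary outcome of scores more than 2 SD below the mean, which the article does not say, most of these children would be counted as above that threshold.

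**Working it through.** **Inputs.** From Sample size: 4-point difference, 90% power, 312 per group, and "assuming a score of 85 (corresponding to –1 SD) and SD of 15 in the control group". From Primary analysis: death scored 55; Wilcoxon-Mann-Whitney test with the Hodges-Lehmann estimate. Assumed, because the documents do not give them: two-sided 5% level, 40% of infants below 28 weeks, strata differing by 5 to 15 points, and 2 to 6% of children per arm untestable because of cognitive impairment.

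**The plan's own figure.** Two means with difference 4 and SD 15 need 296 per arm. Dividing by the Wilcoxon efficiency 3/π gives 310, against 312 stated. Simulated Wilcoxon power at 312 per arm is 91.0%. For recruitment, 624/0.9/0.8 = 866.7, against 868 stated. The sample size reproduces and is not in question.

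**Where an imputed score falls.** With no difference between strata the draws centre on 85, which is 85 − 55 = 30 points above a death. With a gap d between strata, the mean below 28 weeks is 85 − 0.6d:
- d = 5: 85 − 3 = 82, or 27 points above a death.
- d = 15: 85 − 9 = 76, or 21 points above a death.

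Multiple imputation draws values and does not assign the mean. With SD 15:
- At or below 55: Φ((55 − 85)/15) = Φ(−2) = 2.3% with mean 85; Φ((55 − 76)/15) = Φ(−1.4) = 8.1% with mean 76.
- Below 70: Φ(−1) = 16% with mean 85; Φ(−0.4) = 34% with mean 76.

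**Effect on the comparison.** Simulation with 312 per arm and 800 runs per scenario. Tested children are normal with SD 15, and the control mean is 85. Untestable children are either set to 55 or drawn from a normal distribution fitted to all observed scores, ignoring arm, which is not among the named predictors. Deaths, strata and other missing data are left out, and one draw stands in for multiple imputation.

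| Effect in tested children | Untestable, control v intervention | Estimate (power) if set to 55 | Estimate (power) if imputed |
|---|---|---|---|
| 4 | 2% v 2% | 3.99 (88%) | 3.94 (89%) |
| 4 | 5% v 5% | 3.89 (83%) | 3.81 (86%) |
| 4 | 4% v 2% | 4.53 (95%) | 3.91 (89%) |
| 4 | 2% v 4% | 3.44 (75%) | 3.92 (89%) |
| 4 | 6% v 2% | 5.03 (98%) | 3.80 (87%) |
| 4 | 2% v 6% | 2.81 (57%) | 3.79 (88%) |
| 0 | 2% v 6% | −1.15 | −0.09 |

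At equal rates the two treatments of these children differ by 3.99 − 3.94 = 0.05 and 3.89 − 3.81 = 0.08 points. At a 4-point imbalance in rates they differ by 5.03 − 3.80 = 1.23 and 3.79 − 2.81 = 0.98 points, or about 0.25 to 0.3 points per percentage point. A rough check on the mean scale agrees: 0.01 × 30 = 0.3. In children, 2% v 6% of 312 is about 6 v 19.

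**The case against.** **The cause is not stated.** The article names incomplete scores without saying why they are incomplete. A reader might infer that the plan knowingly gives every untestable child an average score. The text does not support that. Some assessments will be incomplete for reasons unrelated to impairment, and imputation suits those. The point is conditional on impairment having prevented testing.

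**Detail is deferred to the SAP.** The primary estimand is given only in brief, and the SAP is not shown. A reader might also infer that the two sections contradict each other. They do not: death is separated from other causes, and Amelia II is described as the general approach. What remains is that the article expressly assigns incomplete scores to imputation. A SAP that scored some of them differently would change a stated rule, so the rule can be judged as written.

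**The reach is limited.** It would be too strong to say that survival with severe impairment scores far better than death. Impaired survivors who complete the test keep their own low scores; only untested survivors are affected. Severe brain injury and the other Bayley-4 scales are also reported as secondary outcomes, so a difference in impairment would not go wholly unseen.

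**A floor score has its own problems.** Inability to test for purely motor, sensory or behavioural reasons does not establish low cognition. Ranking untestable children at or below the lowest tested survivor, yet not below deaths, may also be impossible: under mean 85 and SD 15, 2.3% of scores fall below 55, or 0.023 × 624 ≈ 14 children. Both objections stand and shape the remedy.

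**Conclusion.** The concern holds in conditional form. Where cognitive impairment prevented testing, the stated rule scores the child too high: around 76 to 85 in expectation under the assumptions above, against 55 for a death. No described analysis corrects this. The alternative death score of 40 changes deaths only, the separate estimand drops these children, and the mixed model inherits the rule.

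The size depends on figures that the documents do not give. With equal rates the estimate moves by less than 0.1 point. About 1 point of the 4-point target is hidden only under an assumed imbalance of 4 percentage points, in either direction. A reader might infer that the primary result will be biased; the documents do not show this, because neither the rate nor any imbalance is known. The case for changing the rule is that an imbalance cannot be ruled out in advance and the change is cheap.

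**What to change.** 1. Have the blinded assessor record the reason for each incomplete Bayley-4.
2. Where severe cognitive impairment prevented testing, substitute a prespecified low score no lower than the death score, for example 55, the plan's own value. Do this in the primary analysis, or at minimum in a prespecified sensitivity analysis.
3. Impute assessments that are incomplete for other reasons, including purely motor, sensory or behavioural ones. Add predictors of impairment that the trial already collects: severe intraventricular haemorrhage, periventricular leukomalacia and, where available, the other Bayley-4 scales.
4. If the substitution is primary, report imputation of all incomplete scores as the alternative analysis.

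The cost is one field on the assessment form and a blinded SAP clarification before database lock, which is feasible because Trial status expects primary outcome collection to run to early 2029. For 2-year assessments already done, the reason would have to be recovered from assessors' records without knowledge of allocation. The downside is that the substituted score is a convention, as the death score already is.

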The key limitation for the study is that it is not possible to blind either the carers or the parents or guardians to group assignment, creating a risk of performance bias due to systematic differences in care. The trial design aims to minimise the impact of this limitation through use of blinding the Trial Steering Committee (including the Trial Biostatistician) and all primary outcome assessors to group assignment. A further limitation is the possibility of attrition bias resulting from perceived differences in care resulting from the intervention or influence of lack of equipoise from some carers. The steering committee aims to minimise the risk of attrition bias through ongoing trial education programmes for parents and staff.

If provision of cycled light and noise is proven effective for improving cognitive scores in infants born before 32 weeks gestation without severe adverse effects, this low-cost, easy to implement and maintain intervention could be rapidly implemented as part of routine clinical care and will highlight the potential benefits of developing a circadian care bundle for incorporation into routine neonatal care. The potential benefits of this intervention could translate to millions of premature infants born globally each year and for their families.

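### The stated imputation predictors for the primary outcome omit treatment group, so imputed scores carry no treatment effect and a real effect is modestly diluted

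*Protocol article*

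**What the plan says.** The Primary analysis section compares the arms with an unadjusted Wilcoxon-Mann-Whitney test and reports the Hodges-Lehmann estimate. It treats two kinds of missing score differently. For deaths, "missing primary outcome data due to death will be replaced with a score of 55", with 40 as a sensitivity value. The second kind is everything else, described as "Missing data, including incomplete Bayley-4 scores, scores outside time window and those missing due to LTFU or withdrawal". The rule for this second kind is that such values "will be imputed (Amelia II R package) using prematurity strata and multiple birth as predictors".

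The section also promises a separate estimand that leaves out participants with missing data. The Secondary analysis section, a covariate-adjusted linear mixed model, adopts the same rule: "Missing data will be imputed or substituted as detailed for the primary estimand". The section on non-adherence and missing data names Amelia II as the general tool and leaves documentation for each estimand to the SAP. None of these sections names treatment group as an imputation predictor or says that imputation is done within arm.

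**The concern.** The analysis estimates a difference between arms, but the imputation model as listed has no term for arm. Within each cell of prematurity stratum and multiple birth, a missing child in the intervention arm and one in the control arm have the same expected score. Each imputed pair therefore contributes an expected difference of zero, and the pooled estimate is pulled towards zero.

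The Sample size section defines 4 points as the smallest difference that would change care. A true effect exactly at that threshold would, on average, be reported below it, and the trial would be somewhat less likely to detect it. The same dilution passes to the treatment coefficient of the mixed model, which takes over the imputation unchanged.

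**Working it through.** **Inputs.** From the Sample size section, the target is that "the study has 90% power to detect an absolute median difference in standardised cognitive score on Bayley-4 of at least 4 points". The same section gives 312 evaluable infants per group, a control mean of 85 with SD 15, 10% loss to follow-up and 20% multiple births. Allocation is 1:1. Two-sided alpha of 0.05 is assumed, because the article does not state it.

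**The plan's own figures.**
- A two-sample comparison of means needs n = 2 × (1.960 + 1.282)² × 15² / 4² ≈ 296 per arm. Dividing by the Wilcoxon relative efficiency 3/π gives 310, against 312 stated.
- Power at 312 per arm is 90.2% by formula and 90.4% by Wilcoxon simulation (4,000 runs).
- 624 / 0.9 / 0.8 = 866.7, against 868 stated.

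The sample size reproduces.

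**Expected shrinkage.** Let δ be the true effect, m the imputed fraction (equal in both arms) and μ the control mean in a cell. With 1:1 allocation, the observed scores pooled over arms have mean μ + δ/2, and imputed children in both arms are drawn around that value.
- Intervention mean: (1 − m)(μ + δ) + m(μ + δ/2)
- Control mean: (1 − m)μ + m(μ + δ/2)
- Difference: (1 − m)δ

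With δ = 4, this gives 3.8 at m = 5%, 3.6 at 10% and 3.2 at 20%. If δ = 0, the difference is 0 for every m.

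**Simulation with the Hodges-Lehmann estimate.** Bootstrap normal-linear multiple imputation (similar to Amelia), 10 imputations, Rubin's rules, 312 / 0.9 ≈ 347 infants per arm, 400 runs per setting. Loss is random and equal by arm. Assumed, not from the article: 40% of infants below 28 weeks, a stratum effect of 5 points, a multiple-birth effect of 1 point, and the 5% and 20% missing rates.

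| Imputed | Estimate, arm omitted | Estimate, arm included | Power, arm omitted | Power, arm included |
|---|---|---|---|---|
| 5% | 3.84 | 3.95 | 89% | 89% |
| 10% | 3.63 | 4.00 | 87% | 90% |
| 20% | 3.17 | 4.00 | 71% | 87% |

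The Monte Carlo error of these power figures is about 1.5 to 2.5 percentage points.

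**Simulations with a mean difference instead.** One with 1,500 runs per setting gave, at 10% imputed, 3.56 points with arm omitted and 3.98 with arm included, and power of 87% and 90%. At 20% it gave 3.17 and 3.98 points, and power of 74% and 86%. Another with 3,000 runs and arm omitted gave power of 85% at 10% and 75% at 20%. Under no effect its type I error was 3.6% and 2.0%. With a true 4-point effect, its 95% interval coverage was 96% and 95%.

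**Which fraction applies.** The article's 10% is for loss to follow-up only. Incomplete and out-of-window scores are also imputed, so m could be larger by an amount the article does not give. The window itself differs between sections (22–36 months under Primary outcome, 20–36 months under Primary analysis), so which scores fall outside it is not settled.

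**The case against.** The strongest reply is that this is summary text. The missing-data rules are introduced as brief, the estimand is deferred to the SAP, and the article does not say that the two predictors are the only ones or that the arms are pooled. The SAP, which is not shown, may include arm. That limits what can be asserted: a reader might infer that the trial will certainly impute without arm, and the article does not establish that. But it goes beyond silence. It names a predictor list for the primary analysis, and the list as named gives a diluted estimate.

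Second, the harm is modest and in the conservative direction. This stands. At the only loss rate given, the bias is about 0.4 points and the power loss about 3 to 5 percentage points. The fixed score for deaths is untouched.

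Third, the separate estimand without missing data offers a check. This stands in part: it would be unbiased under random loss, but it is not the primary estimand and is not an exact counterpart, because it also excludes deaths.

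A reader might go further and conclude that imputing is worse than analysing observed cases. The simulations support that only for an imputation without arm and for loss that is random and equal by arm. They say nothing about arm-related loss, which the Discussion has in mind: "A further limitation is the possibility of attrition bias resulting from perceived differences in care". Nor has any bias or power cost been shown for leaving out site, sex, socioeconomic status or other covariates. Auxiliary variables may help less than hoped. The ASQ appears only in the flow-chart caption, and the other Bayley-4 subscales would usually be missing for the same children who are lost.

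**Conclusion.** The point holds as a correction to a stated rule. With the predictors listed, a true 4-point effect would be estimated at about 3.6 points at the planned 10% loss, with power of about 85–87% instead of about 90%. At an assumed 20% imputed, the figures are about 3.2 points and 71–75%, against 86–87% with arm in the model.

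These sizes assume roughly normal scores with SD 15, two-sided alpha of 0.05, loss that is random and equal by arm, and no arm term added in the SAP. Under no effect there is no bias, and type I error was below 5% in simulation. A reader might infer a raised risk of a false positive result or a seriously compromised trial; neither follows. The defect is an avoidable dilution of the primary estimate that is cheap to remove.

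**What to change.** In the Primary analysis section and in the SAP, add treatment group to the predictors of the Amelia II model, or state that imputation is done separately by arm. A masked arm code is enough, so the statistician's blinding is not affected.

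For the mixed model in the Secondary analysis section, also put that model's baseline covariates into the imputation (socioeconomic status, parental risk index, sex, birth weight z-score, antenatal steroid use and site, besides the two predictors already listed), so that imputation and analysis are compatible. Further auxiliary variables are optional.

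The cost is a sentence in the protocol, a few lines of SAP and code, and no new data. It should be settled before database lock.
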